# Group physiotherapy compared to individual physiotherapy to treat urinary incontinence in aging women: study protocol for a randomized controlled trial

**DOI:** 10.1186/s13063-017-2261-4

**Published:** 2017-11-16

**Keywords:** Urinary incontinence, Pelvic floor muscle training, Elderly women

## Abstract

**Background:**

Urinary incontinence (UI), one of the most prevalent health concerns confronting women aged over 60 years, affects up to 55% of older community-dwelling women—20–25% with severe symptoms. Clinical practice guidelines recommend individualized pelvic floor muscle training (PFMT) as a first-line treatment for stress or mixed UI in women, although lack of human and financial resources limits delivery of this first-line treatment. Preliminary data suggest that group-based treatments may provide the answer. To date, no adequately powered trials have evaluated the effectiveness or cost-effectiveness of group compared to individual PFMT for UI in older women. Given demographic projections, high prevalence of UI in older women, costly barriers, and group PFMT promising results, there is a clear need to rigorously compare the short- and long-term effectiveness and cost-effectiveness of group vs individual PFMT.

**Methods/Design:**

The study is designed as a non-inferiority randomized controlled trial, conducted in two facilities (Montreal and Sherbrooke) in the Canadian province of Quebec. Participants include 364 ambulatory, community-dwelling women, aged 60 years and older, with stress or mixed UI. Randomly assigned participants will follow a 12-week PFMT, either in one-on-one sessions or as part of a group, under the supervision of a physiotherapist. Blinded assessments at baseline, immediately post intervention, and at one year will include the seven-day bladder diary, the 24-h pad test, symptoms and quality of life questionnaires, adherence and self-efficacy questionnaire, pelvic floor muscle function, and cost assessments. Primary analysis will test our main hypothesis that group-based treatment is not inferior to individualized treatment with respect to the primary outcome: relative (%) reduction in the number of leakages.

**Discussion:**

Should this study find that a group-based approach is not less effective than individual PFMT, and more cost-effective, this trial will impact positively continence-care accessibility and warrant a change in clinical practice.

**Trial registration:**

ClinicalTrials.gov, NCT02039830. Registered on 12 December 2013; Study protocol version 2; 21 November 2013.

**Electronic supplementary material:**

The online version of this article (doi:10.1186/s13063-017-2261-4) contains supplementary material, which is available to authorized users.

## Background

Urinary incontinence (UI), one of the most prevalent health concerns confronting women aged 60 years and over, affects up to 55% of older community-dwelling women [1]—20–25% having severe symptoms (> 10 UI episodes/week) [1]. Recognized as a serious medical condition, UI is also a social issue, one that engenders shame and negative self-perception leading to reduced social interaction and physical activity [2–4]. It is associated with poor self-rated health, impaired emotional and psychological wellbeing, and impaired sexual relationships [3, 5, 6]. It doubles women’s risk of being admitted to a nursing home, independently of age or the presence of any other co-morbid conditions [7].

Clinical practice guidelines recommend individualized pelvic floor muscle training (PFMT) as a first-line treatment for stress or mixed UI in women (Level A evidence [8–12]); however, inadequate financial and human resources prevent delivery of individualized PFMT in many countries [13–15].

Evidence from two recent randomized controlled trials (RCTs) suggests that group PFMT is effective for treating stress and mixed UI in older women, resulting in high continence rates post-intervention compared to no treatment or bladder training [16, 17]. A group-delivery approach offers an effective way to overcome financial and human resource barriers; moreover, it has been shown to increase participant’s motivation, adherence, and UI self-management capabilities [18–22]. In recent years, the search for less costly forms of rehabilitative treatments has taken on a greater impetus and been subject to intense debate [8, 23, 24]. It is now recognized that for some pathological conditions, group rehabilitation approaches offer a viable solution, one that would permit better allocation of available economic resources—material and human [23]. Additionally, group intervention is already acknowledged, within the field of health promotion, as a powerful tool for promoting behavior modification: group sessions provide greater motivation (by reducing an individual’s sense of isolation) and a forum for providing information (particularly for those too timid to ask questions) and foster peer support and discussions: e.g. Weight Watchers [25]. Tackling UI through group sessions could also prove to be an effective means of educating and encouraging active self-management; therefore, it could have an impact in the longer term. [26, 27] To date, no studies have compared with adequate power the long-term effectiveness or cost-effectiveness of group PFMT to individualized PFMT for the treatment of UI in older women [18].

Given group PFMT’s promising results, there is a clear need to compare the short- and long-term effectiveness and cost-effectiveness of group vs individual PFMT, especially considering demographic projections, the high prevalence of UI in older women and the costly barriers to individualized PFMT. If we demonstrated that group-based treatment is not meaningfully less effective than individualized one-on-one treatment, and more cost-effective, group-based PFM training would be warranted as a first-line UI treatment.

### Rationale for a non-inferiority trial

A non-inferiority design was chosen because: (1) individual PFMT is the standard of care; (2) recent literature and our preliminary data on aging women suggest that group-based PFMT may be effective immediately post treatment and in the short term (less than six months); (3) there is potential for long-term benefits from group-based interventions resulting from increased peer-support and mutual self-help leading to increased compliance with treatment; (4) the anticipated lower cost; and (5) the potential to improve accessibility to care through a group approach (overcoming lack of human and financial resources). Should this study find that a group-based PFM training approach is not meaningfully less effective than individual PFM training, it would warrant a change in clinical practice.

### Objectives

The overall objective of the GROUP (Group Rehabilitation Or IndividUal Physiotherapy for Urinary Incontinence in Aging Women) trial is to determine if group-based PFMT for women aged 60 years and older with stress or mixed UI is not meaningfully less effective, sustainable, and affordable than the currently recommended individualized (one-on-one) PFMT.

The specific objectives are to compare the effectiveness of group-based PFMT vs individualized PFMT on:the % reduction in the number of UI episodes, as measured by the seven-day diary [28], immediately post intervention, and at one year post randomization (primary outcome);lower urinary track symptoms, level of distress, and quality-of-life impact, immediately post intervention and at one year post randomization. These secondary outcomes will be measured by, respectively, the seven-day bladder diary (number of urinary incontinence, number of micturition [28], the 24-h pad test (quantity of urine loss) [29], five modules of the International Consultation on Incontinence Questionnaire (ICIQ): the ICIQ-Urinary Incontinence short form (ICIQ-UI short form) [30], the ICIQ-Nocturia (ICIQ-N) [31], the ICIQ-Lower Urinary Tract Symptoms quality of life (ICIQ-LUTSquol) [32], the ICIQ-Vaginal symptoms (ICIQ-VS) [33], the ICIQ-Female Lower Urinary Tract Symptoms sex (ICIQ-FLUTSex) [34];self-efficacy, immediately post intervention and at one year post randomization, as measured by the Geriatric Self Efficacy scale [35] and the Broom Self Efficacy questionnaire Part A [36];impression of improvement and benefits, immediately post intervention and at one year post randomization as measured by the Patient Global Impression of Improvement (PGI-I) [37] and the Satisfaction and willingness to have another treatment (B&W) [17];PFM strength, function, and morphometry as measured by the digital Oxford scale [38], pelvic floor dynamometry [39], transperineal US [40] immediately post intervention and at one year post randomization.

We will also compare the direct costs of group-based PFMT and individualized PFMT using the adapted Dowell–Bryant Incontinence Cost Index (DBICI) [41] immediately post intervention and at one year post randomization.

## Methods

### Trial design

The present study is a non-inferiority RCT involving two metropolitan areas in the province of Quebec, Canada: Montreal and Sherbrooke. This trial design is based on recommendations outlined in the “Research Methodology” chapter of the *International Consultation on Incontinence* book [42]. It comprises three parallel evaluations at, respectively, pre-intervention, post-intervention (1–2 weeks after treatment will have been completed), and one year post randomization, each involving structured interviews, questionnaires, bladder diary, pad tests, as well as physical and gynecological exams (Fig. 1).

**Fig. 1 Fig1:**
[figure not shown]
Schedule of enrolment, interventions, and assessments

### Research sites

The study is conducted at the research center of the Institut Universitaire de Gériatrie de Montréal and at the research center of the Centre Hospitalier de l’université de Sherbrooke.

### Participants

The target population is older women with stress UI and mixed UI. “Older” is defined as aged 60 years and over; as a cut-off age, this population of post-menopausal women have a UI profile distinctive from that of pre-menopausal or post-partum women [43]. Other RCTs on UI in older women also employ this cut-off age [17, 44]. There is no upper age limit as women as old as 98 years have been cured of UI through PFMT [45]. Participants are classified as incontinent if they report a weekly average of three or more episodes of involuntary urine loss during the preceding three months. This is a validated indicator of UI that has been used in cohort studies and RCTs on UI [16, 44]. Finally, type of UI is confirmed as a pattern of stress/mixed UI on the validated Questionnaire for Incontinence Diagnosis (QUID) [46].

### Recruitment

Women are being recruited from community advertisements, newspaper ads, the Research Center of the Institut Universitaire de Gériatrie de Montréal’s bank of participants, gynecology and urology clinics within the metropolis of the two study centers. In Montreal, these include the gynecology clinic at the Maisonneuve-Rosemont Hospital, and the CHUM gynecology clinics, the CLSC Lucille Teasdale, the CSSS Jeanne Mance. In Sherbrooke, this includes the urology and gynecology clinics at the Centre Hospitalier Universitaire de Sherbrooke. A poster explaining the research project is being displayed at each clinic. Interested candidates are invited to call the research coordinator.

Determination of eligibility is achieved in two steps: (1) telephone eligibility evaluation with a research assistant; and (2) on-site eligibility evaluation with the evaluator. Participant eligibility criteria are described in Table 1. These criteria ensure recruitment of a homogeneous sample of community-based older women with stress/mixed urinary incontinence signs and symptoms. Women excluded from the study are referred back to their healthcare provider to receive standard incontinence care.

**Table 1 Tab1:** Inclusion and exclusion criteria

Inclusion criteria	
- Aged 60 years and over - Have stress or mixed urinary symptoms at least three times a week persisting for three months or more	
- Able to have a gynecological examination	
Exclusion criteria	
- Have a BMI ≥ 35; - Reduced mobility (not able to get around without the aid of a cane, crutches, or a walker) - Suffer from untreated chronic constipation - Experience important organ prolapse (POPQ > 2) - Received physiotherapy treatment for urinary incontinence in the past year - Have a surgery for incontinence or organ prolapse in the past year - Currently taking any medication for urinary incontinence (eligible if comfortable stopping the medication) or medications affecting skeletal muscles - Experiencing any leakage of stool or mucus - Have an active urinary or vaginal infection in last three months - Recent change in hormonal replacement - Any co-morbidities or risk factors interfering with the study (e.g. respiratory, cardiovascular, or memory problems, active cancer, diabetes, etc.)	

### Telephone eligibility evaluation (20 min)

Initial contact is over the phone. A research assistant briefly explains the project. Potential candidates are informed of the study’s objectives and procedures. If interested, they are screened for eligibility using a standardized telephone questionnaire developed and used in our previous studies. The UI type is determined by the QUID over the telephone; it is a six-item self-administered questionnaire developed to identify and differentiate UI types in women [46]. This instrument has shown good internal consistency and test–retest reliability, good content and criterion validity, and good specificity/sensitivity in women with UI [47]. Further, QUID is highly recommended for UI type classification by the International Consultation on Incontinence (Grade A) [47]. When women present with stress or mixed UI, the consent form (Additional file 1) is mailed out to the participant with the seven-day bladder diary [28, 47]; the diary is completed and brought to the evaluator at the onsite eligibility evaluation.

### Onsite eligibility evaluation (1 h)

Women are scheduled for onsite evaluations with a physiotherapist if they report at least three UI episodes on the seven-day bladder diary. After signing the consent form, the Mini-Mental State Examination [48] questionnaire is completed (excludes women with cognitive impairment) and a vaginal exam is conducted to identify any perineal pain or prolapse likely to interfere with either the evaluation or the intervention. Those not eligible for the present study are referred back to their healthcare provider. Eligible participants complete the evaluation and are randomized to either individualized or group PFMT.

### Interventions

The women in both groups receive the same 12-week PFMT, either in one-on-one sessions or as part of a group, under the direction of an experienced physiotherapist trained in pelvic floor rehabilitation. The choice of a 12-week PFMT approach is based on muscle physiology theory: strength-training programs show positive effect after 8–12 weeks [49]. In post-menopausal women, Gunnarsson et al. reported a significant improvement in strength and reduction in UI episodes after 12 weeks of training [50]. Both the one-on-one and group-based PFMT sessions are conducted once a week; participants are deemed to have successfully completed the program if they attended ten or more of the 12 sessions. Although there is no known side effect/complication related to PFMT other than possible discomfort following the intervention, any adverse event is monitored. All participants are instructed to contact research personnel should they experience any adverse event at any point during the study.

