### PFMT sessions

For both groups, the weekly sessions last 1 h and include a 15-min educational period and a 45-min exercise component. The educational period covers the various functions of the PFMs, including pre-contraction and normal bladder control, and voiding parameters: fluids and fluid intake; toilet positions; and voiding dynamics. The exercise component includes PFM strength, endurance, and coordination exercises. Between PFM exercises, lower extremity strength, balance and functional exercises (dance) are performed. This approach is in line with our previous research findings, which indicate that mixed and stress UI older women have reduced PFM and lower-extremity strength and balance as compared to continent women [18, 51, 52]. It is also a component of PFMT programs designed for the elderly [16, 17]. The treatment protocol is divided into three phases allowing for gradual progression in treatment; that is, the gradual addition of increasingly difficult exercises in terms of exercise duration, repetition, and position. Each phase lasts four weeks. See Table 2 for monthly treatment’s exercise details.

**Table 2 Tab2:** Monthly treatment’s exercise details

	Warm-up exercises	Pelvic floor exercises				Core exercises	Dance
		Knack^a^	Maximal contractions^a, b^	Fast contractions	Podiums^c^		
Weeks 1–4	Anterior and posterior pelvic tilts standing (4 reps), plantar flexion and dorsal flexion of the ankle (4 reps bilaterally)	(1 cough only) 3 reps	6 reps, 6-s hold	—	3 reps, 6 s/step	Pull belly button towards spine four-point kneeling (6 reps, hold 6 s), bridge (6 reps, 6 s hold)	3 beginner songs
Weeks 5–8	Simple rotation of the pelvis standing (4 reps), plantar flexion and dorsal flexion of the ankle (4 reps bilaterally)	(2 coughs) 3 reps	8 reps, 8-s hold	2 reps, 8 contractions	3 reps, 8 s/step	Pull belly button towards spine four-point kneeling + contraction of the PFM + lifting of the arm (8 reps, 8-s hold)	3 intermediate songs
Weeks 9–12	“8 shaped” rotation of the pelvis standing (4 reps), plantar flexion and dorsal flexion of the ankle (4 reps bilaterally)	(3 coughs) 3 reps	10 reps, 10-s hold	2 reps, 10 contractions	3 rep, 10 s/step	Pull belly button towards spine four-point kneeling + contraction of the PF+ lifting of one arm (8 reps, 8-s hold), contraction of PFM+ contraction transverse + bridge (6 reps, 8-s hold)	3 advanced songs

^a^The knack involves pre-contracting the PFM before and during a cough

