#### Blinding

Investigators, data analysts, and physiotherapists in charge of outcome evaluations remain blinded to the individual participants trial group allocation. Although participants cannot be blinded to their own group allocation, they are blinded to the study’s hypothesis and to the treatment offered in the alternate group. Despite their different formats, both groups have parallel weekly sessions in terms of content and time, but at different locations and/or on different days. To minimize the risk of assessor’s unblinding, participants are asked (both in the consent form and at the time of each assessment) not to discuss their treatment with the independent assessor. In addition, in each center, the assessment is separated from the intervention session, by both time and location.

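### The only adverse event route described is participant-initiated contact, and the risk statement covers only pelvic floor training, so falls, exercise injuries and vaginal complaints may be under-counted

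*Protocol article*

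**What the plan says.** The Interventions section combines a risk statement with a commitment: "Although there is no known side effect/complication related to PFMT other than possible discomfort following the intervention, any adverse event is monitored". The next sentence gives the only mechanism: "All participants are instructed to contact research personnel should they experience any adverse event at any point during the study". The instruction is the same in both arms and is not limited to the telephone.

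The PFMT sessions section describes a program wider than pelvic floor work: "Between PFM exercises, lower extremity strength, balance and functional exercises (dance) are performed". It justifies this content by earlier findings that "mixed and stress UI older women have reduced PFM and lower-extremity strength and balance as compared to continent women". Table 2 shows the dance component advancing from beginner to advanced songs over the 12 weeks. The Individualized PFMT section and the notes to Table 2 give that arm alone an intravaginal biofeedback probe.

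The Adherence section lists what is asked in connection with the follow-up calls: contact details, incontinence-related consultations, medication, surgery, other health problems that could affect incontinence, and continued exercise. It also has the physiotherapist check each exercise diary weekly. Under Blinding, women are asked "not to discuss their treatment with the independent assessor".

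**The concern.** Under the described route, a woman must first decide that a fall, a strained back or vaginal irritation counts as an adverse event, and then act on it. A risk statement that names only discomfort does not prompt her or the staff to think of the other components. Falls and exercise injuries are foreseeable from balance and dance work in women aged 60 and over with no upper age limit, and local complaints are foreseeable from a probe.

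The trial is intended to support a change in practice from one physiotherapist per woman to one per class of eight. A reader weighing that change will want to know whether the class is as safe. If events are recorded only when volunteered, a low count cannot be told apart from low reporting. The harm record also matters because the main analysis keeps only women who complete the one-year assessment. A woman who leaves because of an injury drops out of that analysis, and the adverse event record is then the natural place for her to appear.

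**Working it through.** The article states no adverse event rate, so there is no figure of its own to reproduce. The check is a comparison of sections, followed by a labelled illustration.

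**1. Does the named risk match the program?**

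| Component | Arm | Covered by the risk statement? |
|---|---|---|
| Pelvic floor exercises | both | yes (discomfort) |
| Lower-limb strength, balance, dance | both | not mentioned |
| Intravaginal biofeedback probe | individual only | not mentioned |

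**2. Which described contact would bring out a fall, strain or vaginal complaint?**

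| Contact | What is described | General harm question described? |
|---|---|---|
| Weekly session, both arms | attendance recorded, diary checked | no |
| Calls at three and six months after the intervention, both arms | consultations, medication, surgery, health problems bearing on incontinence, adherence | no |
| Post-intervention and one-year assessments, both arms | outcome measures, including a vaginal symptoms questionnaire; treatment not to be discussed with the assessor | no |
| Any time, both arms | the participant contacts research personnel | only if she starts it |

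The general route is the last row. The health questions in the second row are tied to incontinence, so a sprain from a dance session falls outside them unless someone judges it relevant.

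**3. What could under-reporting do?** Inputs: 364 women (Sample size calculation), equal allocation, so 364 / 2 = 182 per arm. The 10% true event rate and all capture fractions are assumptions.

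Recorded events per arm = 182 × true rate × capture fraction. True events: 182 × 0.10 = 18.2.

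| Capture, individual / group | Recorded, individual | Recorded, group | Ratio, group / individual |
|---|---|---|---|
| 100% / 100% | 18.2 | 18.2 | 1.00 |
| 50% / 50% | 9.1 | 9.1 | 1.00 |
| 60% / 50% | 10.9 | 9.1 | 0.83 |
| 80% / 40% | 14.6 | 7.3 | 0.50 |

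With equal true rates, the recorded ratio is simply the ratio of the capture fractions. Equal under-reporting lowers both counts and leaves the comparison undistorted. A false difference needs capture to differ by arm.

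**4. What would a count of zero mean?** By the rule of three, zero events among 182 women with full capture puts the upper 95% bound at about 3 / 182 = 1.6%. If only 50% of events are captured (assumed), the bound is 3 / (182 × 0.5) = 3.3%; at 30%, 3 / (182 × 0.3) = 5.5%.

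**The case against.** The strongest reply is that this is a condensed journal article. It says events are monitored without saying how, and forms and scripted questions may sit in the full protocol. That stands as a limit: the article does not show that no one asks. The point rests on what is stated, namely one reporting route, a list of call questions tied to incontinence, and a risk statement narrower than the program.

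The risk picture must also be kept in proportion. Reduced balance is a comparison with continent women, and the exclusion criteria remove those with "Reduced mobility (not able to get around without the aid of a cane, crutches, or a walker" (bracket left open in the extract). Dance and balance work takes place under supervision, so the physiotherapist would see a fall in a session. What can be missed is delayed pain, an injury noticed later, or a problem during unsupervised home exercise. Vaginal symptoms are scored at the assessments, but that records status at fixed times and does not log events during training. The request under Blinding concerns treatment, and does not tell women to withhold health events.

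A reader might infer that harms will be counted unevenly between arms, with fewer reports from the classes. The article does not support that. "Both the one-on-one and group-based PFMT sessions are conducted once a week", the same physiotherapist delivers both formats at a location and is available before and after sessions of both kinds, and the diary check and calls are common to both arms. One-on-one sessions do offer more privacy than a class of eight, where private sessions are optional and capped at three, so a difference is possible. It remains an inference.

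Finally, harm is not a stated objective or outcome, and the non-inferiority test is unaffected. Both statements are true. They limit the weight of the point but do not remove the value of a usable safety record.

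**Conclusion.** The concern holds in a limited form. As described, adverse event collection depends on the participant taking the first step, the scheduled health questions are confined to matters bearing on incontinence, and the named risk does not extend to the balance, dance and probe components. Falls, exercise injuries and vaginal complaints may be under-counted.

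The extent is unknown. The figures of 9 recorded out of 18, and a bound of 3.3% or 5.5% in place of 1.6%, depend wholly on assumed event and capture rates. Differential capture between arms is possible but not established. The primary efficacy conclusion does not depend on any of this. It is an inexpensive improvement to the harm record and to participant safety, and not a flaw that invalidates the design.

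**What to change.** Keep the instruction to contact research personnel and add the same short scripted adverse event question in both arms at contacts that already exist:

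- at the weekly diary check, asked of each woman individually and not in front of the class;
- at the three- and six-month calls;
- at the post-intervention and one-year visits.

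The question should name falls, exercise-related injury or pain, and vaginal or urinary complaints. The treating physiotherapist or the unblinded research assistant should ask it, never the blinded evaluator, because an answer about a probe or a class would reveal the arm. The cost section has a research assistant making the calls, whereas the Adherence section attributes the accompanying questions to evaluators, so the asker needs to be named.

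Report the number of women with each kind of event by arm, and extend the risk statement in the Interventions section to the balance, dance and probe components.

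Cost: a line on the diary-check and call forms, a brief question at two visits, and one table, with no extra visits or staff. More minor complaints will be recorded. With 353 of 364 women already recruited, the question reaches mainly the remaining contacts, so the trial would mix two methods of ascertainment. Solicited and spontaneous events should therefore be reported separately.
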